# Theta-burst rTMS in schizophrenia to ameliorate negative and cognitive symptoms: study protocol for a double-blind, sham-controlled, randomized clinical trial

**DOI:** 10.1186/s13063-024-08106-9

**Published:** 2024-04-17

**Keywords:** Schizophrenia, Theta-burst, Transcranial magnetic stimulation, Negative symptoms, Cognitive symptoms

## Abstract

**Background:**

Treatment effects of conventional approaches with antipsychotics or psychosocial interventions are limited when it comes to reducing negative and cognitive symptoms in schizophrenia. While there is emerging clinical evidence that new, augmented protocols based on theta-burst stimulation can increase rTMS efficacy dramatically in depression, data on similar augmented therapies are limited in schizophrenia. The different patterns of network impairments in subjects may underlie that some but not all patients responded to given stimulation locations.

**Methods:**

Therefore, we propose an augmented theta-burst stimulation protocol in schizophrenia by stimulating both locations connected to negative symptoms: (1) the left dorsolateral prefrontal cortex (DLPFC), and (2) the vermis of the cerebellum. Ninety subjects with schizophrenia presenting negative symptoms and aging between 18 and 55 years will be randomized to active and sham stimulation in a 1:1 ratio. The TBS parameters we adopted follow the standard TBS protocols, with 3-pulse 50-Hz bursts given every 200 ms (at 5 Hz) and an intensity of 100% active motor threshold. We plan to deliver 1800 stimuli to the left DLPFC and 1800 stimuli to the vermis daily in two 9.5-min blocks for 4 weeks. The primary endpoint is the change in negative symptom severity measured by the Positive and Negative Syndrome Scale (PANSS). Secondary efficacy endpoints are changes in cognitive flexibility, executive functioning, short-term memory, social cognition, and facial emotion recognition. The difference between study groups will be analyzed by a linear mixed model analysis with the difference relative to baseline in efficacy variables as the dependent variable and treatment group, visit, and treatment-by-visit interaction as independent variables. The safety outcome is the number of serious adverse events.

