Treatment effects of conventional approaches with antipsychotics, other pharmacological agents, or psychosocial interventions are limited and not clinically significant in reducing negative symptoms and improving social outcomes [4]. Based on the literature review, we can summarize that rTMS, and specifically, theta-burst rTMS (TB-rTMS), can be an excellent opportunity to enhance emotion processing and ameliorate negative symptoms in schizophrenia. However, optimal protocols are to be found. Based on recent genetic findings, it seems that schizophrenia is not a single disease but multiple genetically distinct disorders, in other words, a group of heritable disorders caused by a moderate number of separate genotypic networks associated with several distinct clinical syndromes [18]. Accordingly, several different brain networks (e.g., default mode network, cortico-cerebellar-thalamic-cortical circuit) are impaired in schizophrenia, while none are impaired in all patients [19, 20]. This different pattern of network impairments in subjects may underlie that some but not all patients responded to a given stimulation location. Taken together these evidences, we propose an augmented theta-burst stimulation protocol in schizophrenia by stimulating both locations connected to negative symptoms, namely the vermis of the cerebellum and the left DLPFC. While the temporoparietal area can also be considered a potential stimulation target, we excluded this target since this location is primarily connected to positive symptoms [21], and we intend to focus on negative symptoms. Besides multi-location stimulation, based on the recent findings on augmented protocols, we intend to deliver 1800 pulses daily to each location, which is 3600 pulses daily compared to the 600 pulses of standard theta-burst protocols. To our knowledge, this would be the first study applying multi-location (DLPFC and cerebellum) augmented theta-burst stimulation in schizophrenia.

The major target of the study is to confirm the safety and efficacy of our augmented protocol of theta-burst TMS in schizophrenia. We aim to confirm the beneficial effects of rTMS treatment on multiple aspects of the disorder such as (1) clinical aspect in terms of PANSS negative score, (2) social cognition such as Theory of Mind (ToM), (3) neurocognition such as cognitive flexibility, and (3) safety in terms of detected serious adverse events (SAEs).

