Negative symptom severity correlates closely with functional outcome, and these symptoms respond the least to antipsychotic medication. Therefore, the need for new effective treatments is extremely important. Based on recent meta-analyses [10, 22], we hypothesize that decrease in PANSS negative score will be significantly larger in the active stimulation group compared to the sham group.

Social cognition impairment is a key domain in schizophrenia related to negative symptoms and affects daily functioning and quality of life [2, 23, 24]. The “Reading the Mind in the Eyes Test (RMET)” and the faux-pas test are sensitive measures of theory of mind and social cognition in schizophrenia. We expect a significantly larger improvement in the active stimulation group relative to the sham group in the RMET total score and in the correct answers in the Faux pas test.

Cognitive flexibility is severely impaired in schizophrenia, and the Wisconsin Card Sorting Test (WCST) is a widely used measure of it. There is strong evidence that cognitive flexibility measured by WCST is correlated with negative symptom severity [25] in schizophrenia. Therefore, we plan to compare the change in WCST performance regarding perseverative errors between study groups. We expect a larger improvement of cognitive flexibility in the active stimulation group. Furthermore, a computational model of the WCST will be used, and the following reinforcement parameters will be estimated: R (reward sensitivity), P (punishment sensitivity), and D (choice consistency) [26, 27].

Several previous investigations in depression [28] and schizophrenia [29] showed that theta-burst rTMS is safe and well-tolerated. However, this will be the first study with multiple location (vermis and l-DLPFC) stimulation. Therefore, it is crucial to monitor adverse events and confirm the safety of this new procedure. Based on previous studies, the most common side effect is a mild headache, while the most serious is an epileptic seizure. However, the latter is very uncommon (1/10,000 treatment sessions). Our hypothesis regarding safety is that there will be no difference between study groups in terms of serious adverse events (SAEs). In case of a serious adverse event, patient will discontinue the treatment and will be unblinded.

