### Withdrawal of patient from study

Patients may withdraw from the study at any time and for any reason without prejudice to their future medical care by the investigator or at the study site. Every effort should be made to keep patients in the study. The reasons for patients not completing treatment and/or the reasons for patients not completing the study will be recorded. A patient may be withdrawn from the study for any of the following reasons:Noncompliance with the protocol or significant protocol violation.A serious or intolerable AE(s)Lost to follow-up.The patient withdraws consent.New antipsychotic or antidepressant medications have to be given during the study

A worsening of the disease does not in itself imply a withdrawal, however, hospitalization due to worsening of symptoms (i.e., psychotic episode) is an SAE that implies a dropout. If a patient reports any intolerable AE, there is no possibility to decrease stimulation intensity, in such cases patient must be withdrawn. The need for a new antipsychotic or antidepressant medication also implies a dropout.

When a patient withdraws from active participation in the study, the reason(s) for discontinuation shall be recorded by the investigator on the relevant page of the eCRF. Whenever possible, all patients who discontinue treatment or withdraw from the study prematurely will undergo all assessments at the early withdrawal visit. Patients who fail to return for final assessments will be contacted by the site in an attempt to collect final data. The investigator should show due diligence and explore all possible options to reach a patient who fails to attend a visit. The investigator must document all attempts to contact the patient in the medical records/source documents (at least 3 documented approaches, via phone, e-mail, or regular mail). It is vital to obtain follow-up data on any patient withdrawn because of an AE. In the event that a patient has to be withdrawn from the study due to a serious adverse event, the patient should be followed until the condition is stabilized or the event is no longer considered clinically significant. In every case, efforts must be made to undertake protocol-specified, safety, and follow-up procedures. If patients are unable or unwilling to return for this follow-up visit, the site will document their efforts to bring the patients in through two documented telephone calls and a registered letter.

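### The only named safety outcome, the number of SAEs, cannot register mandatory withdrawals for intolerable non-serious effects and mixes illness-related hospitalization with stimulation-specific events

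*Protocol article*

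**What the plan says.** Safety is tied to serious adverse events in three places, and they agree.

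- Abstract, Methods: "The safety outcome is the number of serious adverse events".
- Background, aims: the fourth aspect of the disorder and its treatment to be examined is "safety in terms of detected serious adverse events (SAEs").
- Background, hypotheses: the expectation is that the arms will not differ on SAEs.

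The same Background section explains why safety matters here. This is the first study to stimulate both sites, so "it is crucial to monitor adverse events and confirm the safety of this new procedure". It also says what to expect: "the most common side effect is a mild headache, while the most serious is an epileptic seizure", with seizure put at 1 per 10,000 treatment sessions.

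Two rules under Withdrawal of patient from study bear on what the outcome can capture. For an intolerable AE, "there is no possibility to decrease stimulation intensity, in such cases patient must be withdrawn". For relapse, "hospitalization due to worsening of symptoms (i.e., psychotic episode) is an SAE that implies a dropout", whereas worsening without hospitalization does not by itself lead to withdrawal.

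The article also provides for recording reasons for discontinuation in the eCRF, for reporting AEs to the authority, and for a safety analysis set. It attaches no outcome other than SAEs to any of these.

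**The concern.** Confirming safety is part of the study's stated main aim, so the outcome on which safety is judged matters. Two features of the SAE count weaken it for that purpose.

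First, it cannot register poor tolerability. The protocol foresees that some patients will find stimulation intolerable and must stop. Unless the event also meets the definition of serious, the patient contributes nothing to the safety outcome. The side effect named as most common, mild headache, is likewise invisible to it.

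Second, it is a mixture. Hospitalization for psychotic worsening and a stimulation-induced seizure each add one to the same total. If seizures are as rare as the article says, illness-related hospitalization could make up much of the count, and a single total would not show which kind of event lies behind it.

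Followed as written, the trial could report that its safety hypothesis was met while appreciably more active than sham patients had to stop because they could not tolerate the treatment.

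**Working it through.** **Plan figures.** The article gives no safety calculation to reproduce. Its exposure figure does reproduce: 20 days × 2 blocks × 1,800 stimuli = 72,000. With 90 patients randomized 1:1 there are 45 per arm.

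**Step 1: what each type of event adds to the named outcome.**

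| Event | Consequence in the article | Adds to SAE count |
|---|---|---|
| Seizure (assumed to be classed as serious) | Treatment stopped, patient unblinded | Yes |
| Hospitalization for psychotic worsening | Dropout | Yes |
| Intolerable AE, not serious | Withdrawal required | No |
| Mild headache, tolerated | None stated | No |
| Worsening without hospitalization | Not in itself a withdrawal | No, unless serious on other grounds |

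The third row is the gap: the protocol acts on the event, and its safety outcome does not see it.

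**Step 2: how many seizures the count would contain.** Expected number = active-arm sessions × 1/10,000. Chance of at least one = 1 − (1 − 1/10,000)^sessions. The article does not say whether a session is a treatment day or a block, so both are shown.

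- By day: 45 × 20 = 900 sessions; 900/10,000 = 0.09 expected; chance of any = 8.6%.
- By block: 45 × 20 × 2 = 1,800 sessions; 1,800/10,000 = 0.18 expected; chance of any = 16.5%.

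Both assume that all 45 patients complete treatment and that the quoted rate applies to this more intensive schedule. On those terms the one stimulation-specific serious event that the article names will probably not occur at all.

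**Step 3: what the outcome could miss.** The article gives no rate of intolerable AEs, so these counts are illustrative only. Suppose no SAEs occur, no sham patient is withdrawn for an intolerable non-serious AE, and k of 45 active patients are.

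| k active vs 0 sham | Active proportion | Fisher exact p (two-sided) | Named safety outcome |
|---|---|---|---|
| 4 | 4/45 = 8.9% | 0.117 | 0 vs 0 |
| 5 | 5/45 = 11.1% | 0.056 | 0 vs 0 |
| 6 | 6/45 = 13.3% | 0.026 | 0 vs 0 |
| 7 | 7/45 = 15.6% | 0.012 | 0 vs 0 |

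For 6 vs 0 the risk difference is 13.3 percentage points (Newcombe 95% CI 2.8 to 26.2). Six is the smallest count against zero that reaches p < 0.05. The table does not predict such a result. The last column is what matters: it stays at 0 vs 0 whatever k is.

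**Step 4: how much an absence of SAEs would say.** With 0 of 45 patients, the one-sided 95% upper limit for the SAE risk is 1 − 0.05^(1/45) = 6.4%. Even for serious events, a clean result is limited reassurance; for tolerability it is none.

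**The case against.** The strongest reply is that SAEs are a legitimate headline safety measure, used consistently, and that the article does not neglect other AEs. It calls for monitoring them, records why patients stop, treats follow-up of AE withdrawals as essential, reports AEs to the authority and defines a safety set. Tables of AEs and withdrawals by arm are commonly left to an analysis plan, and none is shown here. This reply stands against any reading that AE data are ignored: a reader might infer that, but the documents do not say so. It does not answer the narrower point, because the safety outcome and hypothesis are stated in the article rather than left open, and they rest on SAEs alone.

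A reader might also infer that psychotic relapse is charged to the device. The text does not support that. Only worsening that leads to hospitalization is classed as an SAE, nothing attributes it to stimulation, and SAEs are compared between randomized arms, so background relapse enters both. Pooling can dilute the comparison; it does not bias it. Nor should psychotic hospitalization be taken out of the safety conclusion: with a first dual-site protocol, that would presume that stimulation cannot provoke it.

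Three smaller objections also stand. The 6 vs 0 split has no source, and the article describes theta-burst stimulation as well tolerated. Seizures would be just as rare under any wider outcome. And since an SAE ends treatment, counts of events and of patients will nearly coincide, so moving to patients is mainly for clarity.

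**Conclusion.** The point holds in a limited form and should be acted on. The sole named safety outcome cannot register patients whom the protocol itself requires to be withdrawn for intolerable, non-serious AEs, and it combines illness-related hospitalization with stimulation-specific events. A result of no difference in SAEs would therefore not support a claim that the dual-site protocol is safe and tolerated.

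The size of the first gap cannot be estimated from the documents, because they give no rate of intolerable AEs. That the named outcome is blind to such withdrawals follows from the definitions and needs no assumption. On the second, about 0.09 to 0.18 seizures are expected in the active arm, given full completion and the quoted rate. The stronger readings, that AE data are discarded or that relapse is treated as device harm, are not supported.

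**What to change.** Restate the safety outcome wherever it appears (Abstract, aims, safety hypothesis) as a short set of measures, each by arm in the safety analysis set and each counted as patients:

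1. patients with at least one SAE, in total and split into hospitalization for psychotic worsening and all other SAEs;
2. patients withdrawn for an AE;
3. patients with any AE, with headache shown separately.

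Give risk differences with 95% confidence intervals for each. Base the safety statement on all of them, with psychotic worsening kept in.

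The cost is small: changed wording, a few more tables, and a safety summary of several numbers instead of one. Reasons for discontinuation are already captured in the eCRF and the safety set is already defined. No dose, withdrawal rule or other clinical procedure is affected.

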**Discussion:**

This is a double-blind, sham-controlled, randomized medical device study to assess the efficacy and safety of an augmented theta-burst rTMS treatment in schizophrenia. We hypothesize that social cognition and negative symptoms of patients on active therapy will improve significantly compared to patients on sham treatment.

**Trial registration:**

The study protocol is registered at “ClinicalTrials.gov” with the following ID: NCT05100888. All items from the World Health Organization Trial Registration Data Set are registered. Initial release: 10/19/2021.

**Supplementary Information:**

The online version contains supplementary material available at 10.1186/s13063-024-08106-9.

## Background

Schizophrenia is a major mental disorder that affects approximately 1% of the population worldwide. Social cognition impairments and negative symptoms such as blunted affect or emotional withdrawal strongly contribute to the psychosocial functioning deficits and long-term disability in schizophrenia [1]. The state-like and trait-like components of social cognition are impaired in schizophrenia [2, 3].

The effect of current antipsychotic medications on social cognition and negative symptoms is strongly limited [4]. Therefore, the significance of non-pharmacological treatments in schizophrenia, such as rTMS, is emerging. Transcranial magnetic stimulation (TMS) is a noninvasive form of brain stimulation in which a changing magnetic field is used to cause an electric current at a specific brain area through electromagnetic induction. While evidence for the efficacy of rTMS treatment in depression is solid and led to FDA approval in 2008, findings on rTMS treatment in schizophrenia are somewhat controversial. Some results show improvement, especially in facial expression recognition and social cognition applying a standard high-frequency (10 Hz) stimulation protocol on the left DLPFC [5]. Some other approaches trying to decrease negative symptoms were unsuccessful [6]. Similarly, the results of other studies applying the same standard 10 Hz stimulation protocol on the temporoparietal cortex to ameliorate auditory hallucinations were also contradictory since some studies showed positive results [7], while others failed to find evidence compared to sham stimulation [8].

Studies applying rTMS to improve negative symptoms in schizophrenia have typically targeted the dorsolateral prefrontal cortex (DLPFC), which is based on neuroimaging findings of reduced DLPFC activation in patients with negative symptoms (e.g., [9]) and emotion processing. A meta-analysis found that rTMS stimulation of the left DLPFC is more effective than sham in treating negative symptoms of schizophrenia. However, the evidence was found to be low quality [10]. The mean weighted effect size compared to sham stimulation was 0.64 (0.32–0.96; *k* = 22, total *N* = 827). Studies with younger participants showed more substantial effects than those with older participants.

The recognition of the role of the cerebellum in schizophrenia pathology termed “cognitive dysmetria” is not new [11]. Furthermore, there is emerging evidence that the brain network consists of the DLPFC, and the vermis of the cerebellum is impaired in schizophrenia. The stimulation of the vermis can lead to the amelioration of negative symptoms [12, 13]. In a recent study, Brady et al. [12] stimulated the cerebellum of patients in a combined TMS-fMRI study. They showed that the improvement in DLPFC-Cerebellar functional connectivity was strongly correlated with the decrease in PANSS negative symptom severity.

Besides the stimulation location, the number of (daily) delivered pulses can also be the key to efficacy. A recent study showed that 61% of non-responders to repetitive transcranial magnetic stimulation (rTMS) responded with further treatment [14], suggesting that FDA-approved protocols may be underdosing. In previous research, 1,800 pulses have produced long-lasting changes in cortical excitability (15) and optimally produced the intended cellular changes [15]. There is also emerging clinical evidence that new, augmented protocols based on theta-burst stimulation can increase rTMS efficacy dramatically in depression. These protocols almost double the response and remission rates in depression by using intermittent theta-burst stimulation (3 pulses of stimulation are given at 50 Hz, repeated every 200 ms, and a 2-s train of TBS is repeated every 10 s). Still, delivering 1200, 2400, or even 18,000 stimuli daily compared to the standard 600 stimuli [16, 17]. Such augmented protocols have not been tested in schizophrenia yet.

Treatment effects of conventional approaches with antipsychotics, other pharmacological agents, or psychosocial interventions are limited and not clinically significant in reducing negative symptoms and improving social outcomes [4]. Based on the literature review, we can summarize that rTMS, and specifically, theta-burst rTMS (TB-rTMS), can be an excellent opportunity to enhance emotion processing and ameliorate negative symptoms in schizophrenia. However, optimal protocols are to be found. Based on recent genetic findings, it seems that schizophrenia is not a single disease but multiple genetically distinct disorders, in other words, a group of heritable disorders caused by a moderate number of separate genotypic networks associated with several distinct clinical syndromes [18]. Accordingly, several different brain networks (e.g., default mode network, cortico-cerebellar-thalamic-cortical circuit) are impaired in schizophrenia, while none are impaired in all patients [19, 20]. This different pattern of network impairments in subjects may underlie that some but not all patients responded to a given stimulation location. Taken together these evidences, we propose an augmented theta-burst stimulation protocol in schizophrenia by stimulating both locations connected to negative symptoms, namely the vermis of the cerebellum and the left DLPFC. While the temporoparietal area can also be considered a potential stimulation target, we excluded this target since this location is primarily connected to positive symptoms [21], and we intend to focus on negative symptoms. Besides multi-location stimulation, based on the recent findings on augmented protocols, we intend to deliver 1800 pulses daily to each location, which is 3600 pulses daily compared to the 600 pulses of standard theta-burst protocols. To our knowledge, this would be the first study applying multi-location (DLPFC and cerebellum) augmented theta-burst stimulation in schizophrenia.

The major target of the study is to confirm the safety and efficacy of our augmented protocol of theta-burst TMS in schizophrenia. We aim to confirm the beneficial effects of rTMS treatment on multiple aspects of the disorder such as (1) clinical aspect in terms of PANSS negative score, (2) social cognition such as Theory of Mind (ToM), (3) neurocognition such as cognitive flexibility, and (3) safety in terms of detected serious adverse events (SAEs).

Negative symptom severity correlates closely with functional outcome, and these symptoms respond the least to antipsychotic medication. Therefore, the need for new effective treatments is extremely important. Based on recent meta-analyses [10, 22], we hypothesize that decrease in PANSS negative score will be significantly larger in the active stimulation group compared to the sham group.

Social cognition impairment is a key domain in schizophrenia related to negative symptoms and affects daily functioning and quality of life [2, 23, 24]. The “Reading the Mind in the Eyes Test (RMET)” and the faux-pas test are sensitive measures of theory of mind and social cognition in schizophrenia. We expect a significantly larger improvement in the active stimulation group relative to the sham group in the RMET total score and in the correct answers in the Faux pas test.

Cognitive flexibility is severely impaired in schizophrenia, and the Wisconsin Card Sorting Test (WCST) is a widely used measure of it. There is strong evidence that cognitive flexibility measured by WCST is correlated with negative symptom severity [25] in schizophrenia. Therefore, we plan to compare the change in WCST performance regarding perseverative errors between study groups. We expect a larger improvement of cognitive flexibility in the active stimulation group. Furthermore, a computational model of the WCST will be used, and the following reinforcement parameters will be estimated: R (reward sensitivity), P (punishment sensitivity), and D (choice consistency) [26, 27].

Several previous investigations in depression [28] and schizophrenia [29] showed that theta-burst rTMS is safe and well-tolerated. However, this will be the first study with multiple location (vermis and l-DLPFC) stimulation. Therefore, it is crucial to monitor adverse events and confirm the safety of this new procedure. Based on previous studies, the most common side effect is a mild headache, while the most serious is an epileptic seizure. However, the latter is very uncommon (1/10,000 treatment sessions). Our hypothesis regarding safety is that there will be no difference between study groups in terms of serious adverse events (SAEs). In case of a serious adverse event, patient will discontinue the treatment and will be unblinded.

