### Design, subjects, and power analysis

We are planning a double-blind sham stimulation-controlled study with two randomized study groups. Since there were previous studies with theta-burst stimulation in schizophrenia, this is a phase II medical device study to evaluate the clinical performance of the theta-burst rTMS protocol in schizophrenia. This superiority study will compare clinical performance in terms of efficacy and safety to sham stimulation. Ninety patients meeting the DSM-V [33] criteria for schizophrenia will be enrolled in the study. Based on a recent meta-analysis on rTMS of the frontal cortex for improving negative symptoms [10], we assumed an effect size of 0.64. Using this assumption and incorporating the baseline value as a covariate, we calculated that the probability is equal to or greater than 90% (beta = 0.90) to find a significant (alpha = 0.05) difference between study groups in negative symptom improvement with this sample size (SAS PROC GLMPOWER). Patients will be assigned to the active and the sham group in a 1:1 ratio by an adaptive randomization algorithm implemented in R [34]. The algorithm took age, sex, education, and negative PANSS score into account. Patient enrolled into the study will receive sequential patient codes, while treatment (active vs. sham) will be assigned to these codes. Patients from the outpatient care of the Department of Psychiatry and Psychotherapy, Semmelweis University will be enrolled who met all the inclusion and none of the exclusion criteria. An enrollment period of 30 months is planned, therefore approximately three subjects need to be included per month to reach the target sample size. Based on the patient flow in the outpatient unit we can screen 4–5 subjects and enroll three subjects monthly. Inclusion criteria are (1) diagnosis of schizophrenia or schizoaffective disorder; (2) clinically stabilized on antipsychotic: a stable dose of antipsychotic medication for > 4 weeks; (3) age 18–55 years, and (4) presence of negative symptoms (based on PANSS): a negative subscore ≥ 16 points and one of items N1–N7 scoring ≥ 4 or two items N1–N7 scoring ≥ 3. The exclusion criteria are (1) any significant neurological illness; (2) intellectual disability; (3) history of head injury with loss of consciousness for more than 1 h; (4) history of epileptic seizures or epileptic activity on the baseline EEG (evaluated by an expert in clinical EEG and epilepsy); (5) alcohol or drug abuse within the past 3 months; (6) depressive episode or antidepressant treatment in the past 4 weeks; (7) ECT in the medical history; (8) implanted pacemaker, implanted drug pump, cochlear implant, implanted defibrillator, implanted neurostimulator or any other TMS incompatible implanted metal device; (9) skin surface is severely injured in the stimulated region of the skull; (10) sclerosis multiplex; (11) pregnancy; (12) severe sleep deprivation; (13) severe heart failure; (14) increased intracranial pressure; (15) intreated migraine; and (16) severe positive symptoms interfere with cognitive tests.

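### Safety is to be confirmed by finding no difference in serious adverse events, but with no margin and about 45 patients per arm that cannot exclude a moderate excess risk

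*Protocol article*

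**What the plan says.** In the Background, the aim is stated as "The major target of the study is to confirm the safety and efficacy of our augmented protocol of theta-burst TMS in schizophrenia". The same section notes that this is the first study to stimulate both sites, and continues: "Therefore, it is crucial to monitor adverse events and confirm the safety of this new procedure". It then gives the hypothesis: "Our hypothesis regarding safety is that there will be no difference between study groups in terms of serious adverse events (SAEs").

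The Methods paragraph of the abstract names the measure: "The safety outcome is the number of serious adverse events". The section on design, subjects and power analysis sets the frame: "This superiority study will compare clinical performance in terms of efficacy and safety to sham stimulation". It fixes the size ("Ninety patients meeting the DSM-V [33] criteria for schizophrenia will be enrolled in the study", allocated 1:1) from an effect size of 0.64 on negative symptoms.

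No equivalence or non-inferiority margin, overall SAE rate or precision target is given for safety. A safety analysis set is defined. The statistical analysis section describes models for the PANSS negative score and the cognitive and social cognitive outcomes, and no test of SAEs.

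**The concern.** A hypothesis of no difference is a null hypothesis. In a superiority comparison the data can reject it or fail to reject it, and failing to reject does not establish it. To support a claim of safety, a trial needs either a margin that the confidence interval must exclude, or an interval reported as an estimate and read for what it rules out. The article offers neither, yet it makes confirmation of safety half of its main aim.

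The safety conclusion itself is at stake. The active arm receives 3,600 pulses a day against the 600 the article calls standard, at two sites not previously combined in this way. The section on data management and monitoring provides for no data monitoring committee and no interim analysis, so the final safety statement will carry much of the weight. If the stated hypothesis is taken at face value, similar SAE counts would be reported as support for safety even where the true risk is moderately higher.

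**Working it through.** **The plan's own figure.** The only power statement is at least 90% for the efficacy endpoint. With 90/2 = 45 per arm and d = 0.64, the noncentrality is 0.64 × √(45/2) = 3.04, which gives 85% power by a two-sided t test at 0.05 without a covariate. Adjusting for baseline with correlation ρ divides d by √(1 − ρ²), and power reaches 90% at ρ of about 0.38. The article does not state ρ, but the claim is reproducible under a modest value. Nothing in it concerns SAEs.

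**Inputs for safety.** About 45 per arm follows from the stated total and ratio; the adaptive randomization may make the arms slightly unequal. The article gives no overall SAE rate, so every rate below is an assumption. The 0.05 is taken as two-sided.

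**1. Chance of detecting an excess.** Power is the sum, over all pairs of counts (i, j), of Bin(i; 45, p_sham) × Bin(j; 45, p_active) for the pairs where Fisher's exact p ≤ 0.05.

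| Sham rate | Active rate | Power |
|---|---|---|
| 2% | 6% | 2% |
| 2% | 10% | 15% |
| 5% | 10% | 6% |
| 5% | 15% | 23% |
| 5% | 20% | 48% |
| 5% | 25% | 71% |
| 5% | 30% | 86% |
| 10% | 20% | 18% |

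In counts: with no sham patient having an SAE, 6 of 45 active patients (13%) are needed for p ≤ 0.05. With two sham patients, 9 of 45 (20%) are needed.

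**2. What equal counts leave open.** The Newcombe interval combines the Wilson limits of the two arms. For 2/45 = 4.4% the Wilson limits are 1.2% and 14.8%. The half-width for the difference is √[(4.4 − 1.2)² + (14.8 − 4.4)²] = 10.9 percentage points. The same method gives ±9.5 points for one patient in each arm and ±7.9 for none in either.

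**3. What zero events leave open.** For 0/45 the exact upper limit is 1 − 0.025^(1/45) = 7.9% (two-sided 95%), or 1 − 0.05^(1/45) = 6.4% (one-sided 95%).

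**4. How far a margin would help.** For non-inferiority with equal true rates p, margin m, one-sided 0.025 and 80% power, n per arm = 2p(1 − p)(1.96 + 0.84)²/m². A 5-point margin needs 124 per arm at p = 2% and 299 at 5%. A 10-point margin needs 31 at 2%, 75 at 5% and 142 at 10%. The available 45 would suffice only with a wide margin and a low rate.

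**5. The hazard the article calls most serious.** For seizures it says "the latter is very uncommon (1/10,000 treatment sessions"). The active arm has 45 × 20 = 900 treatment days, or 1,800 blocks if each block counts as a session. At that rate the chance of at least one seizure is 1 − 0.9999^900 = 8.6%, or 1 − 0.9999^1800 = 16.5%. Seeing none would therefore say little about whether the rate had changed. This is a side calculation only, because the seizure rate is not the overall SAE rate.

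**The case against.** The strongest reply is that the article never commits the error. It plans no significance test on SAEs, and the Background speaks of significantly larger effects for the PANSS and social cognition outcomes but not for safety. A reader might infer that the trial will declare the protocol safe when p exceeds 0.05. No such rule is written, and the analysis may be set out in a plan that is not shown. This stands, and it limits the point to the objective and hypothesis. Those are stated here, and an analysis plan cannot turn no difference without a margin into evidence of safety.

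Three other strong readings also fail.

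- That a finding of safety would follow almost whatever the truth is too much: power is 71% for 5% against 25% and 86% for 5% against 30%. The insensitivity is to moderate excesses.
- That SAEs are bound to be rare is not supported: the section on withdrawal counts hospitalization for a psychotic episode as an SAE, so the rate could be well above that of seizures.
- That other harms go unrecorded is wrong: the article calls for adverse event monitoring and reporting and records reasons for withdrawal, including intolerable events. Wider safety tables may sit in the analysis plan.

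It is also fair that a phase II trial is normally sized on efficacy, and that the safety expectation rests partly on earlier theta-burst studies. Neither is disputed. The sample size is not the fault; the claim attached to it is.

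**Conclusion.** The point holds as a fault in the stated objective, hypothesis and superiority framing for safety. Without a margin, absence of an SAE difference at about 45 per arm does not confirm safety. If the sham rate is 5%, a doubling would be detected about 6% of the time and a tripling about 23%. Equal low counts (none to two patients per arm) leave excesses of roughly 8 to 11 percentage points compatible with the data. The power figures rest on assumed SAE rates, a two-sided 0.05 and equal arms; the interval widths depend on the counts observed. Large excesses would probably be seen. The point should be corrected because it changes what the trial may conclude on one of its two main aims. It does not touch the primary efficacy analysis, the sample size or data collection.

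**What to change.** In the Background and in the section on design, subjects and power analysis, replace the aim of confirming safety, the no-difference hypothesis and the superiority framing for safety with an estimation objective. Keep superiority for efficacy.

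For the safety analysis set, report the number and percentage of participants with at least one SAE in each arm with exact 95% confidence intervals, and the risk difference with its 95% interval. Word the conclusion as the largest excess risk that the data exclude, and say beforehand that none in 45 would still allow a rate of up to 7.9%. Adverse events and adverse-event withdrawals, which the trial already records, can be summarised alongside.

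The cost is rewording and a small table, with no extra patients or data collection. The downside is a more modest safety claim.
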